## 4.1 General objective

To determine whether screening pregnant women for malaria with RDTs may detect placental infection and predict risk of poor birth outcomes due to malaria in areas of varied malaria transmission in Africa.

Specific primary objectives:

1. To compare the results of RDTs, microscopy and PCR performed on peripheral blood from women in the second and third trimesters of pregnancy in malaria-endemic areas of Africa.
2. To determine the positive and negative predictive values of results of RDTs, microscopy and PCR performed on peripheral blood from women in the second and third trimesters of pregnancy, as compared with evidence of placental infection by histological examination after delivery.

Specific secondary objectives:

1. To measure and compare the frequency of pregnancy outcomes (infant birth weights, maternal hemoglobin), prevalence of placental malaria, and risk of symptomatic malaria among women in the study cohort. Participants who test positive by RDT at the time of usual IPTp administration will receive artemisinin-combination treatment (ACT) or quinine; participants who test negative by RDT will receive standard-of-care IPTp with SP.
2. To collect samples for future laboratory analyses related to malaria in pregnancy, including the measurement of the prevalence of molecular markers of antimalarial resistance in the study cohorts.
3. **STUDY DESIGN**

(See Figure 1 on next page.) Women will be enrolled at their initial presentation for antenatal care after quickening, i.e. on the first antenatal visit when they are eligible for IPTp according to WHO recommendations.2 On the usual IPTp schedule, typically once in the second and once in the third trimester, blood will be collected from all participants for RDT testing, preparation of thick and thin smears for light microscopy, and PCR. RDTs detecting histidine-rich protein 2 (HRP2) and plasmodium lactate dehydrogenase (pLDH) will be used for testing. All participants with negative RDT results will receive SP, and those with a positive RDT result will receive ACT or quinine (according to national policy for treatment of malaria in pregnancy). All participants will be followed up to delivery. At delivery maternal peripheral and placental blood samples will be collected for RDT testing, light microscopy, and PCR, and placental tissue samples will be processed for histopathological examination. Measurement of maternal hemoglobin and infant birth weight will be obtained.

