**Subsequent routine antenatal visit/s**

(≥ 1 month after previous visit and before onset of labor)

- History & clinical exam
- Venous blood for Hb, RDTs, thick/thin smear, and storage in EDTA, red cell pellet and filter paper for PCR
- Provision of other standardized care (ITN, iron + folate supplementation, etc) according to national guidelines

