**Follow up at delivery**

- Maternal peripheral blood for Hb, RDTs, smear, and PCR
- Placental blood for RDTs, smear, and PCR
- Placental tissue sample to process for histopathological examination
- Measurement of infant birth weight
- (Other data on any maternal or fetal morbidity/mortality)

1. **STUDY POPULATION**

Participants in this evaluation will include pregnant women presenting for routine antenatal services in areas of Africa where IPTp is considered standard of care according to WHO and national malaria control program guidelines. Pregnant women of any parity will be eligible for enrollment. Anticipated sites include antenatal clinics in Burkina Faso, Nigeria, and Uganda. Specific participant selection criteria will include (please see also section 7.2 on participant enrollment):

1. Presenting for care after quickening and before onset of labor (i.e. in the second or third trimester of pregnancy)
2. Age between 16 years and 44 years, inclusive
3. Willingness and ability to follow up with study visits and activities through the duration of pregnancy and at delivery
4. Absence of history of serious adverse reaction to sulfa drugs
5. Absence of history of serious adverse reaction to artemisinin-based drugs or quinine (depending on national policy on treatment of malaria in pregnancy)
6. Absence of HIV infection (both because guidelines for malaria prevention in pregnancy for HIV-infected women differ from those for HIV-negative women, and in order to avoid confounding of pregnancy outcomes by HIV-related complications or treatments in this early evaluation)
7. Absence of history of or current obstetrical complications (e.g. pre-eclampsia, eclampsia, hypertension during pregnancy, post-partum hemorrhage, evidence of multiple gestation)
8. Absence of chronic disease (e.g. diabetes mellitus, sickle cell disease)
9. Absence of evidence of severe acute disease requiring inpatient management or referral
10. Provision of written informed consent
11. Enrollment Hb ≥7 g/dL

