***Uganda site-specific information (as requested by WHO; italic font):*** *The usual standard of care for the care and follow-up of pregnant women at TDH follows national guidelines from the Uganda Ministry of Health. Pregnant women are provided, for free according to resource availability, with a standard antenatal care package, including access to the four recommended antenatal visits for basic assessment, symptomatic management (empiric treatment of urinary tract infections and sexually transmitted diseases, analgesics for pain syndromes, and similar), hemoglobin estimation where available, iron and folate supplementation, antihelminth treatment, routine counseling and testing for syphilis and HIV, a long-lasting insecticide-treated bed net (LLIN), and advice and counseling on nutrition and on prevention of sexually transmitted diseases. The standard of care for any medical problem that exceeds the capacity of the participating center is to refer to a higher level of care. Participants in this study will be assured access to components of the basic antenatal package including routine assessment by health center staff, iron and folate supplementation, and a LLIN. As clearly described during the informed consent discussion, symptom management and referral will be done at the discretion of the health center staff. As discussed with the Uganda ethical review committee (Makerere University Faculty of Medicine Research and Ethics Committee), study staff including a clinician may assist with providing standard care to study participants in case of need and in collaboration with health center staff.*

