***(End Uganda site-specific information.)***

*7.3.5 Scheduling of subsequent visit/s*

The participant will be encouraged to return to the study site for her subsequent routine antenatal visit/s, and if feasible, for any intervening care-seeking. Subsequent antenatal visits will be scheduled according to the national standard of care, typically including at least one visit in the second trimester and one visit in the third trimester. Routine visits will be scheduled at least 4 weeks apart; participants will not receive more than one dose of SP within any 4-week period. Each participant will be given a card/booklet with dates of future study visits, and in which to record any care or treatment that is received from non-study site providers between routine visits.

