**7.4 Study activities at subsequent routine antenatal visits**

*7.4.1 Clinical data collection*

At each subsequent scheduled antenatal visit, information will be collected from the participant on any treatments sought since the previous visit and on current symptoms, and a brief clinical assessment will be performed by a health center staff clinician.

*7.4.2 Laboratory sample collection*

Study staff will collect blood from participants for use in study laboratory procedures, and will prepare the samples and conduct the diagnostic tests described; all other care will be provided by health center staff (i.e. clinicians, typically midwives and nurses, employed by the health center). At each scheduled visit, the participant will provide a 2 mL (two milliliter) venous blood sample for HemoCue Hb measurement, preparation of two RDTs, preparation of thick and thin smears for light microscopy, and storage in a microtainer and on filter paper for PCR (see further details in section 7.6 below). Hb and RDT results will be used in clinical management as in sections 7.4.3 and 7.6.1 below; microscopy and PCR results will not be immediately available and will not be used in management.

*7.4.3 Administration of antimalarial medicines*

If both RDT results are negative, the participant will receive a complete dose of SP by DOT. If one or both RDTs are positive, she will receive a complete curative dose of ACT or quinine (as in section 7.3.3 above); the initial dose will be given by DOT, and the remaining doses will be given to the participant with clear instructions for completing the regimen at home. SP or ACT/quinine will be administered by health center clinical staff. If a patient receives curative treatment with ACT or quinine, a return visit (or home visit by study staff) to administer a dose of SP will be scheduled for 2 weeks after the end of the curative treatment. (See section 7.3.3 for explanation of rationale.)

*7.4.4 Provision of symptomatic and routine antenatal care*

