**11.2 Analysis plan**

The unit of analysis will be each pregnancy. For each pregnant woman a complete data set consists of the following:

| Variable | Type of data | Variable classification | | | | |
| --- | --- | --- | --- | --- | --- | --- |
| Confounder | Evidence of placental malaria | Outcome measure | | |
| Predictive value of diagnostic | Infant birth weight | Maternal Hb |
| RDT on peripheral blood taken during 2nd trimester | Binary (positive / negative) |  |  | X |  |  |
| Microscopy of peripheral blood taken during 2nd trimester | 1. Binary (positive / negative)  2. Count for positives |  |  | X |  |  |
| PCR on peripheral blood taken during 2nd trimester | Binary (positive / negative) |  | X |  |  |  |
| RDT on peripheral blood taken during 3rd trimester | Binary (positive / negative) |  |  | X |  |  |
| Microscopy of peripheral blood taken during 3rd trimester | 1. Binary (positive / negative)  2. Count for positives |  |  | X |  |  |
| PCR peripheral blood taken during 3rd trimester | Binary (positive / negative) |  | X |  |  |  |
| RDT on peripheral blood taken during or shortly after delivery | Binary (positive / negative) |  |  | X |  |  |
| Microscopy of peripheral blood taken during or shortly after delivery | 1. Binary (positive / negative)  2. Count for positives |  |  | X |  |  |
| PCR result on peripheral blood taken during or shortly after delivery | Binary (positive / negative) |  | X |  |  |  |
| Placental histology for evidence of infection | Binary (positive / negative) |  | X |  |  |  |
| Diagnostic results of any additional visits to clinic (eg symptomatic infection) | Binary (positive / negative) |  | X |  |  |  |
| Maternal Hb at delivery | Continuous |  |  |  |  | X |
| Infant birth weight at delivery | Continuous |  |  |  | X |  |
| Study site | Nominal | X |  |  |  |  |
| Age | Continuous | X |  |  |  |  |
| Gravidity | Ordinal | X |  |  |  |  |
| SP treatment | Binary (yes/no) | X |  |  |  |  |
| Iron & folate supplementation | Binary (yes/no) | X |  |  |  |  |
| Bed net use | Binary (yes/no) | X |  |  |  |  |

The following definitions will be used:

- Evidence of placental malaria: a positive PCR result is obtained for any peripheral blood sample and / or there is evidence of placental infection by histology
- RDT positive: a positive RDT result is obtained from one or more blood samples
- Microscopy positive: parasites are detected by microscopy (thick film) in one or more of the blood samples

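### Section 11.2 calls a woman positive on any sample but does not hold the number of test rounds constant, so the accuracy figures partly reflect how often women were tested

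*Protocol*

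**What the plan says.** Section 11.2 makes the pregnancy the unit of analysis, so a woman's repeated tests collapse to one result. The RDT is positive when "a positive RDT result is obtained from one or more blood samples". The reference, evidence of placental malaria, is positive when "a positive PCR result is obtained for any peripheral blood sample", when histology shows infection, or both. The variable table describes a complete data set with three peripheral time points: second trimester, third trimester and delivery. It also places diagnostic results from additional clinic visits on the reference side.

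The number of rounds per woman is left open elsewhere:
- Section 6 admits women "Presenting for care after quickening and before onset of labor", so a late enrollee has no second-trimester round.
- Section 5 sets the nominal pattern: "On the usual IPTp schedule, typically once in the second and once in the third trimester, blood will be collected from all participants".
- Section 7.3.5 follows each country's standard of care and states a minimum interval but no maximum number: "Routine visits will be scheduled at least 4 weeks apart". Figure 1 gives a similar interval, "≥ 1 month after previous visit and before onset of labor".
- Section 7.4.2 takes samples every time: "At each scheduled visit, the participant will provide a 2 mL (two milliliter) venous blood sample for HemoCue Hb measurement, preparation of two RDTs".
- Section 7.3.4, for Uganda only, mentions usual care "including access to the four recommended antenatal visits for basic assessment".
- Section 7.6.8 accepts partial delivery data, for example maternal blood without a placenta.

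Negative predictive power is the first primary outcome (section 11.1). Section 11.2 reports sensitivity, specificity, PPV and NPV for all samples combined and for each location.

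**The concern.** Under an any-positive rule, a woman's RDT result can only move from negative to positive as tests are added, and so can the peripheral PCR part of the reference. Two women with the same infection history and the same RDT can be classified differently because one was seen more often. If visit patterns differ between countries, a difference in accuracy between sites may be partly a difference in visit counts. The reader would take it for a difference in how the RDT performs under different transmission.

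The confounder list in section 11.2 includes study site but not the number of tests. Adjusting for site does not deal with variation between women within a site, and an estimate for one location carries that location's own testing frequency. Nor is there a rule for a woman seen twice in one trimester, who has two results for a single binary slot.

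**Working it through.** **Inputs.**
- Sensitivity 65% and specificity 98% come from section 11.3, which does not say whether they are per test or per woman. Section 3.1.2 reports a similar 65% and 99% against PCR on the same blood sample, so I take them as per test. That is an assumption.
- Rounds k, counting delivery: 2 (late enrollee, one antenatal round), 3 (the nominal design) and 5 (four antenatal visits; an upper bound, since the Uganda text speaks only of access to four).
- Prevalence 25% for a fixed reference: section 3.1.1 gives about one in four at delivery without prevention.
- PCR positivity q per round is not in the protocol. I assume 10%, with 5% as a check.

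The protocol gives no figure for the any-positive measure. Its site sample sizes cannot be reproduced because the site prevalences are not stated; their sum, 345 + 460 + 860 = 1,665, is right.

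**Specificity.** A reference-negative woman stays RDT negative only if every test is negative: 0.98^k. This gives 0.98² = 0.960, 0.98³ = 0.941 and 0.98⁵ = 0.904.

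**Case A: infection status fixed, independent test errors, prevalence 0.25.** Sensitivity = 1 − 0.35^k. For k = 2, PPV = 0.25×0.8775 / (0.25×0.8775 + 0.75×0.0396) = 0.881 and NPV = 0.75×0.9604 / (0.75×0.9604 + 0.25×0.1225) = 0.959.

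**Case B: new, independent infection each round; reference positive on any PCR; q = 0.10.** Reference prevalence = 1 − 0.9^k. Per round, P(RDT negative and PCR negative) = 0.98×0.90 = 0.882, and P(RDT negative) = 0.882 + 0.35×0.10 = 0.917. Then NPV = (0.882/0.917)^k and PPV = 1 − (0.9^k − 0.882^k)/(1 − 0.917^k).

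| | k = 2 | k = 3 | k = 5 |
|---|---|---|---|
| Specificity (A and B) | 0.960 | 0.941 | 0.904 |
| A: sensitivity | 0.878 | 0.957 | 0.995 |
| A: PPV | 0.881 | 0.844 | 0.775 |
| A: NPV | 0.959 | 0.985 | 0.998 |
| B: reference prevalence | 0.190 | 0.271 | 0.410 |
| B: sensitivity | 0.669 | 0.686 | 0.720 |
| B: PPV | 0.798 | 0.813 | 0.839 |
| B: NPV | 0.925 | 0.890 | 0.823 |

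With q = 0.05, case B gives NPV 0.963, 0.946 and 0.911.

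**Between the extremes.** If infection risk varies between women so that the within-woman correlation is 0.6 (mean 10%, simulated), NPV is 0.962, 0.964 and 0.967, which is almost flat, while PPV falls 0.749, 0.722, 0.673.

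**Correlated RDT errors shrink case A.** At 20% prevalence with independent errors, PPV for three rounds is 0.2×0.9571 / (0.2×0.9571 + 0.8×0.0588) = 0.803, and for five rounds 0.2×0.9947 / (0.2×0.9947 + 0.8×0.0961) = 0.721. With error correlation 0.3 the two values are 0.832 and 0.797.

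**Not modelled:** histology in the reference, and treatment. Every woman gets SP, or curative treatment followed by SP, after each antenatal round, which changes what later rounds can find.

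**The case against.** The strongest reply is that the variable table fixes the design: three slots per woman, so k = 3. As the nominal design that is correct, and it narrows the problem to women with an empty slot, women with more than one visit in a slot, and additional visits. It does not remove the problem, because the definitions speak of any sample and no sentence restricts the analysis to complete sets.

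Second, any-positive over the screening schedule is a legitimate measure of a repeated-screening strategy, which is what the study is meant to inform. I agree, and it should stay. It needs a stated schedule, or a stated treatment of departures from it, to be interpretable.

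Third, the effect on NPV may be close to nil, as the intermediate case shows. That stands.

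Fourth, handling of missing or extra rounds could be left to a statistical analysis plan. That is fair for the detail, but the any-positive rules themselves are fixed here.

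A reader might go further in two ways that the protocol does not support:
- That the effect could not be corrected after the study. There are separate forms for day 0, subsequent visits and delivery (Appendices D to F). Each RDT result goes on the patient's data form (section 7.6.2.4), and treatments given are recorded at each visit (sections 7.3.4 and 7.4.4). Test counts can be derived from these.
- That sections 5 and 7.4 contradict each other on the testing schedule. Section 5 describes a typical pattern, section 7.3.5 words its own pattern as typical too, and the four-week rule is a minimum gap, not a monthly schedule.

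**Conclusion.** The point holds in a limited form. As written, section 11.2 lets the number of rounds vary under any-positive rules for both the test and the reference, so all four accuracy measures depend in part on testing frequency, overall and by location.

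The clearest effect is on specificity: about 96%, 94% and 90% for two, three and five rounds, if 98% is a per-test value and errors are independent. Correlated errors would make the drop smaller. For NPV, the first primary outcome, neither direction nor size can be stated: it rises if infections persist, falls if they are new each round, and can be nearly flat in between. A reader might infer that the primary NPV result is materially distorted; the protocol gives no basis for that. How far sites will differ in visits per woman is also unknown.

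This is a worthwhile, low-cost improvement and not a flaw that invalidates the study. Coding SP as yes/no, which cannot separate one dose from several in the birth weight and Hb models, is a separate minor matter.

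**What to change.** In section 11.2:
1. Add per-trimester (or per-test) accuracy from the marginal models already planned, clustered on the woman, against two references that do not grow with visits: PCR on the same sample, and placental histology, the reference named in primary objective 2.
2. Keep the any-positive result beside it, labelled as the measure of repeated screening.
3. State how women with missing or extra rounds enter the any-positive classification, for example with a sensitivity analysis limited to the three slots, and say which result fills a slot when there are two visits in one trimester.
4. Tabulate the number of test rounds per woman by site from the existing visit forms.

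The cost is a few sentences and slightly more data handling and analysis. No visits, samples or participants are added.

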If both RDT results are negative, the participant will receive a complete dose of SP by directly observed therapy (DOT) on the day of enrollment. If one or both RDTs are positive, she will receive a complete curative dose of ACT or quinine according to the national policy for treatment of parasitemia in pregnancy; the initial dose will be given by DOT, and the remaining doses will be given to the participant with clear instructions for completing the regimen at home. SP or ACT/quinine will be administered by health center clinical staff. If a patient receives curative treatment with ACT or quinine a return visit (or home visit by study staff) to administer a dose of SP will be scheduled for 2 weeks after the end of the curative treatment. The rationale for use of both curative treatment and SP-IPTp for RDT-positive women is as follows: The mode of action of IPTp is not yet completely understood, but is presumed to be two-fold: an IPTp dose *treats* existing asymptomatic infections, and also *prophylaxes* against new infections due to the long half-life of the drug used (e.g. SP). There is some evidence that the primary benefit may result from “intermittent suppressive chemoprophylaxis.”50 Quinine does not have such a prophylactic effect, and while ACTs pair a short-acting artemisinin compound with a longer-acting drug, there is as yet no evidence that ACTs provide a prophylactic effect similar to SP in pregnancy. Therefore, we believe that the safest approach for the current study is to provide both curative treatment, and the currently recommended IPTp drug, i.e. SP. While there are no published data that raise concern for clinically significant drug interactions among these antimalarials, for reasons of tolerability and due to the limited data on pharmacokinetics in pregnant populations we will administer the drugs 2 weeks apart.

*7.3.4 Provision of symptomatic and routine antenatal care*

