**11.1 Study outcome measures**

Results of peripheral blood tests performed during gestation will be analyzed for associations with evidence of placental malaria and pregnancy outcomes. The statistical analysis will focus on three primary outcomes: 1) negative predictive power of malaria RDTs, peripheral blood films and PCR performed on peripheral blood to diagnose placental malaria during gestation, 2) association of placental malaria during gestation on mean infant birth weight and 3) association of placental malaria during gestation on mean maternal Hb. These outcomes will be used to assess the potential utility of RDTs as screening tests to identify clinically significant malaria infections at a time when effective preventive measures may be taken. Other factors known to influence the study outcomes, including iron and folate supplementation, bed net use and administration of antihelminthic drugs will be treated as confounders in the analysis. In addition, stratified analysis will be conducted to assess these associations within subgroups based on geographic location, estimates of malaria endemicity, participant age, and parity (gravida class).

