The accuracy of RDTs and peripheral microscopy at detecting placental malaria will be assessed by considering the sensitivity, specificity, positive predictive value and negative predictive value of each diagnostic compared to evidence of placental malaria. This analysis will be conducted for all samples combined and also separately for each study location. Marginal generalized linear models will be developed to assess the impact of confounders on predictive values.

The impact of RDT screening and treatment compared to standard IPT on infant birth weight and maternal Hb will be assessed for non-inferiority by testing the hypotheses:

1. Mean birth weight of infants whose mothers were RDT positive & treated with ACT/quinine ≥ mean birth weight of infants whose mothers were RDT negative (and received SP)
2. Mean Hb of mothers who were RDT positive & treated with ACT/quinine ≥ mean Hb of mothers who were RDT negative (and received SP)

Standard statistical techniques such as t-tests, ANOVA and regression modeling will be used to test these hypotheses and investigate the potential impact of confounders on birth weight and maternal Hb.

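### Section 11.2 announces a non-inferiority comparison with standard IPT, but the protocol has no unscreened IPT group and the hypotheses carry no margin

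*Protocol*

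**What the plan says.** Section 11.2 of the protocol sets the aim: "The impact of RDT screening and treatment compared to standard IPT on infant birth weight and maternal Hb will be assessed for non-inferiority". Two hypotheses follow. The first is an inequality of average infant weights, by the mother's group: "RDT positive & treated with ACT/quinine ≥ mean birth weight of infants whose mothers were RDT negative (and received SP"). The second concerns maternal haemoglobin: "Mean Hb of mothers who were RDT positive & treated with ACT/quinine ≥ mean Hb of mothers who were RDT negative (and received SP"). The methods named are t-tests, ANOVA and regression, with attention to confounders.

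The study design text that follows the objectives in section 4 explains how the groups arise. On the IPTp schedule, "blood will be collected from all participants for RDT testing", and then "All participants with negative RDT results will receive SP, and those with a positive RDT result will receive ACT or quinine". Section 7.3.3 adds SP for RDT-positive women two weeks after the end of curative treatment, with the reason that "we believe that the safest approach for the current study is to provide both curative treatment, and the currently recommended IPTp drug". Section 7.4.3 repeats this for later visits.

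Section 11.1 lists birth weight and Hb among three primary outcomes and frames the first as "association of placental malaria during gestation on mean infant birth weight". Sections 2 and 4 place both outcomes under secondary objective 1, whose task is to measure and compare them in the cohort.

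**The concern.** A comparison of screening with standard IPT needs women managed by standard IPT, that is, given SP without a screening test, whether infected or not. The protocol has none. The two groups in the hypotheses are the two branches of a single strategy, separated by a test for infection.

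A shortfall in RDT-positive women could reflect infection that preceded treatment, and would say nothing about whether screening does worse than IPT. A null result could be reported as non-inferiority to an approach that was never compared. Section 13 says the study is meant to supply data for later evaluations of screening and targeted treatment as an alternative to IPTp, so a mislabelled result of either kind would matter.

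The form of the test is a second problem. Non-inferiority needs a stated margin and a confidence limit judged against it. A plain inequality tested by a difference test is either almost impossible to establish or too easy to pass, depending on how it is read.

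**Working it through.** **1. The comparison**

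| Element | Needed for a comparison with standard IPT | What the protocol provides |
|---|---|---|
| Comparator | Women given SP without screening | None; all participants are tested |
| Allocation | Randomised, or at least unrelated to infection | The woman's own RDT result |
| Drug contrast | Screening strategy against SP alone | Both groups are scheduled for SP; RDT-positive women also receive curative treatment |
| Comparability | Similar infection status | Groups are split on a test for infection |

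Section 3.1.1 describes placental malaria as clearly associated with low birth weight, and says younger women and those with few pregnancies are at higher risk. Regression on age, gravidity, bed nets and the other listed factors may reduce confounding by those factors. It cannot recover the effect of screening against IPT, because no RDT-positive woman is left on IPT alone.

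**2. The plan's own figure**

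Section 11.3 says the study can detect 85 g in birth weight and 0.34 g/dL in Hb. It gives no SD, RDT-positive share or sidedness for these, so they cannot be strictly reproduced. With 1,665 × 0.85 = 1,415 evaluable women and the usual two-sample formula, δ = SD × (z_α + z_power) × √(1/n₁ + 1/n₂), 85 g at 80% power and 5% corresponds, for an assumed SD of 450 g, to about 19% RDT-positive (two-sided) or 14% (one-sided). Over assumed SDs of 400-500 g the range is 11-26%. The figure is therefore plausible for an ordinary difference test. Nothing in section 11.3 presents it as a margin.

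**3. Standard error implied by 85 g**

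Assumption: 85 g is detectable with 80% power at 5%. Section 11.3 attaches those levels only to the PPV/NPV hypothesis.

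- Two-sided: SE = 85 / (1.960 + 0.842) = 30.3 g.
- One-sided: SE = 85 / (1.645 + 0.842) = 34.2 g.
- Two funded sites (345 + 860 = 1,205 women), with the same SD and RDT-positive share: multiply by √(1665/1205) = 1.175, giving 35.7 g and 40.2 g.

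**4. Reading A: the inequality must be demonstrated**

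At true equality, the chance of rejecting a null of lower or equal mean is the one-sided significance level: 2.5% or 5%.

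**5. Reading B: a non-significant result counts as non-inferior**

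P(pass | true deficit d) = 1 − Φ(d/SE − z_α).

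| True deficit | Three sites, two-sided | Three sites, one-sided | Two sites, two-sided | Two sites, one-sided |
|---|---|---|---|---|
| 50 g | 62% | 57% | 71% | 66% |
| 85 g | 20% | 20% | 34% | 32% |

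For example, for 50 g, two-sided, three sites: 50/30.3 − 1.960 = −0.31, and 1 − Φ(−0.31) = 0.62. Losing a site raises the pass rate, so this reading rewards imprecision.

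**The case against.** Several objections carry weight.

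- *RDT-negative women do receive the standard IPTp drug.* True: sections 2 and 4 say so. A reader might infer that nobody gets standard IPT, and that is too strong. What is missing is an unscreened IPT group. RDT-negative women are selected by a negative test and do not represent all women under IPT.
- *The contrast is not strictly infected against uninfected.* Also true. At the 65% sensitivity used in section 11.3, some RDT-negative women are infected. The contrast is RDT-positive against RDT-negative.
- *A margin may be in an analysis plan that is not shown.* Possible. But the protocol writes the hypotheses out without one, and no margin would turn this contrast into a comparison with IPT.
- *Sections 11.1 and 11.2 already plan for confounders.* They do, and that supports an adjusted association. It does not supply the missing comparator.
- *A deficit in RDT-positive women is informative.* It is: the general objective includes predicting poor birth outcomes. So the result is not worthless either way; only the label attached to it is wrong.
- *The placental-malaria analysis in section 11.1 is a legitimate separate analysis.* Agreed. A different exposure there is not an error.
- *These outcomes are secondary in sections 2 and 4, and the repair is only wording.* Both are true, but section 11.1 calls them primary, and the wording at fault defines the conclusion to be drawn.

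**Conclusion.** The point stands. As written, section 11.2 promises an inference that the design cannot give, and its hypotheses are not in a form that tests non-inferiority. The first part follows from the protocol's text and needs no numerical assumption.

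The sizes are illustrative: 2.5-5% success at equality under one reading; under the other, 57-62% passes at a 50 g deficit and about 20% at 85 g with three sites, more with two. They rest on reading 85 g as detectable with 80% power at 5%. The protocol does not say which hypothesis is the null, so both readings are possibilities and neither is plan text.

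A reader might go further and say that the roughly 123 g in section 11.3 makes failure almost certain. The documents do not support this. The figure is called a likely change, with no direction and no groups, so it is not a stated deficit in treated RDT-positive women. A failure rate above 99% would also require an 85 g margin that the plan does not contain. Under reading B with three sites, a 123 g deficit would fail about 98% of the time: 123/30.3 − 1.960 = 2.09, a pass rate of 1.8% (2.5% one-sided).

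**What to change.** 1. In section 11.2, delete the comparison with standard IPT and the non-inferiority claim, and replace the two inequalities with an estimation statement. For instance: *the difference in mean birth weight and in mean maternal Hb at delivery between RDT-positive (treated) and RDT-negative women will be estimated by regression, adjusted for the listed confounders, and reported with a 95% confidence interval as an association within a cohort managed by screening.* This matches secondary objective 1.
2. Do not adopt 85 g and 0.34 g/dL as margins. They are detectable differences without a justification as margins.
3. Keep the placental-malaria association in section 11.1, but reconcile its primary label for birth weight and Hb with their secondary status in sections 2 and 4.

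The cost is protocol wording. Enrolment, procedures and data collection do not change. What is given up is a claim about IPT that could be tested only with a concurrent, preferably randomised, unscreened IPT group and a justified margin.
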